### Safety and monitoring

The assessment of safety will be based mainly on the frequency of adverse events, which includes all serious adverse events. Adverse events will be summarized by presenting the number and percentage of patients having any adverse event. Any other information collected (e.g. severity or relatedness to study medication) will be listed as appropriate. An independent data safety monitoring board will regularly review the safety data, efficacy data and the events of interest. Monitoring will be executed in compliance with the guideline “Quality Assurance of research involving human subjects 2.0” of “The Netherlands Federation of University Medical Centers” [22]. Intensive monitoring for this study will be performed by an independent and qualified monitor of the Service Desk Clinical Research Office of the University Medical Centre Groningen.

### Statistical analysis

The data from all centers will be pooled and summarized with respect to demographic and baseline characteristics and efficacy and safety observations. Exploratory analyses will be performed using descriptive statistics. The primary outcome variable ‘successful transplantation’ will be analyzed using a generalized mixed model, adjusting for stratum (A/B) and center. Data will be presented for the complete intention-to-treat population (all patients having taken at least one dose of study medication), as well as the per-protocol population (all patients who completed the study without major protocol deviations). For missing data we will perform regression based multiple imputation.

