## Background

### Background and rationale

Elderly patients are an important and growing part of both the dialysis and kidney transplant population. In 2019, 30 % of the newly transplanted kidney transplant recipients in the Netherlands were above 65 years of age, while more than 60 % of the dialysis population was above 65 years of age. These elderly kidney transplant recipients (KTR) have different risk profiles when compared with younger KTR. Whereas graft loss in younger patients is mainly due to loss of the transplant, graft loss in elderly patients is predominantly associated with patient’s death with a functioning graft. Thus, death censored graft loss amongst elderly KTR is a relatively rare phenomenon [1, 2]. There are two important explanations that account for this difference.

First, the incidence of rejection amongst elderly KTR is lower; the aging immune system renders the elderly patient less prone to rejection [1, 3]. This decreased propensity for rejection is explained by senescence of adaptive immunity with decreasing telomere length of immune cells and a shift from a naïve T cell repertoire towards more terminally differentiated memory T cells [4]. Additionally, a shift towards an increasing proportion of CD28^‒^ T cells has been noted [5, 6].

Second, a higher competing incidence of death amongst elderly KTR is observed; mostly because these patients have increased rates of mortality associated with cardiovascular complications, infection, and malignancy [2, 7–11].

Besides recipient characteristics, donor characteristics are also important determinants of outcome in KTR. The Eurotransplant Senior Program (ESP) allocates kidneys within a narrow geographic area from donors aged ≥ 65 years to recipients ≥ 65 years regardless of HLA, thereby minimizing cold ischemia time [12]. Therefore, poor kidney transplant function in these elderly KTR may be related to chronic injury of the kidney prior to transplantation due to older donor age, and to an increased susceptibility of these kidneys to the (nephron-)toxicity of calcineurin inhibitors (CNIs) [13], the cornerstone of current immunosuppressive regimens.

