### Outcomes

#### The primary endpoint

This study will evaluate two immunosuppressive regimens in elderly KTR in two strata with adapted endpoints based on the expected outcome according to donor characteristics. Both strata will be analyzed together for the primary endpoint.

The primary endpoint will be “successful transplantation”, which is defined as survival with a functioning allograft with an estimated GFR (eGFR) above 30 (stratum A) or 45 (stratum B) ml/min per 1.73 m^2^ at two years after transplantation. We chose to stratify the endpoint for donor type as a substantial proportion of kidney function after transplantation is determined by donor type, and we.

only expect medication-related modification of kidney function within this donor-related predetermined potential of the transplanted kidney.

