#### Secondary endpoints

The main secondary endpoint is the primary endpoint analyzed separately per stratum.

Other secondary objectives include assessment at months 12 and 24 of death, graft loss and eGFR below 30 or 45 ml/min/1.73m^2^.

Secondary endpoints include the incidence of (biopsy-proven) rejection, presence of and changes in immunosenescence, frailty and co-morbidities, and assessment of and changes in health-related quality of life as a patient-reported outcome. All endpoints will be analyzed in both the complete study population and the separate strata.

Safety objectives include standard assessments of (serious) adverse events (including drug-related adverse events and drug-related discontinuation of study medication), and specific objectives regarding clinically relevant infections, post-transplantation diabetes mellitus, malignancy and cardiovascular events. In Table 2 a complete overview of the study endpoints is depicted. Finally, a cost-effectiveness analysis will also be performed.

To assess immunosenescence we will assess the immunological phenotype pre-transplant and identify T cell ageing characteristics that are associated with the risk for acute rejection and infection after kidney transplantation. We also will assess immunological ageing within a two year period after kidney transplantation in relation to the two different immunosuppressive regimens.

See Table 2 for a complete overview of the endpoints.

**Table 2 Tab2:** Primary and secondary endpoints of the OPTIMIZE study

	Endpoint	Determination of endpoint
**Primary endpoint**	‘successful transplantation’	At 24 months after transplantation: survival with a functioning allograft with an estimated GFR above 30 (stratum A) or 45 (stratum B) ml/min per 1.73 m^2^.
**Main secondary endpoint**	Primary objective, analyzed separately per stratum	-
**Other secondary endpoints**	Incidence of individual endpoints of death, graft loss, eGFR below 30 or 45 ml/min/1.73m^2^	At 12 and 24 months after transplantation
	Evolution of renal function over time by slope analysis	eGFR and creatinine clearance, based on the 24 hour excretion of creatinine in the urine
	Incidence of treated biopsy-proven rejection (tBPAR)	Will be checked and recorded at every study visit
	Rejection treatment and type of rejection treatment	Will be checked and recorded at every study visit
	Development of donor-specific anti-HLA antibodies	At 12 and 24 months after transplantation: DSA as measured by Luminex

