All procedures will follow standard procedures, except biobanking. For this purpose, extra blood samples will be withdrawn, at baseline, and 6, 12 and 24 months after transplantation. These will be stored in a biobank. A special part of the biobank is the collection of isolated Peripheral Blood Mononuclear Cells (PBMCs); this will we done for 250 patients. The PBMCs will be used for study of immunosenescence.

Several instruments, both objective and subjective, will be used to measure frailty, cognitive and physical functioning, health-related quality of life, illness perceptions, symptom burden and adherence to immunosuppressive medication of the KTR’s in this study. See Additional file 1 I for more information regarding tests and questionnaires.

Loss to follow-up virtually does not exist in the transplant population. If patients withdraw their informed consent, we will ask their permission to obtain a creatinine value and dialyses information at months 6, 12 and 24. Patients that discontinue their randomized study regimen (for more than 21 days) will remain in the study.

All study data will be entered into the secured OPTIMIZE project database. This database complies with the standards of Good Clinical Practice.

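### As worded, the per-protocol set drops patients who die before month 24, although death is a failure of the primary endpoint

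*Protocol article*

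**What the plan says.** The Statistical analysis section names two sets. The first is given as "Data will be presented for the complete intention-to-treat population (all patients having taken at least one dose of study medication"; the second is "the per-protocol population (all patients who completed the study without major protocol deviations". Neither is named as the primary set, and the article does not define completion.

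Under The primary endpoint, success at two years is "defined as survival with a functioning allograft with an estimated GFR (eGFR) above 30 (stratum A) or 45 (stratum B" ml/min per 1.73 m². A patient who has died cannot meet this. The table of endpoints confirms it by listing the components of failure separately: "Incidence of individual endpoints of death, graft loss, eGFR below 30 or 45 ml/min/1.73m^2".

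The last study visit is at month 24. On follow-up, Study procedures and data management says "Loss to follow-up virtually does not exist in the transplant population" and "Patients that discontinue their randomized study regimen (for more than 21 days) will remain in the study".

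**The concern.** Whether a patient is in the per-protocol set depends on completing the study, and completing a 24-month study depends on being alive at month 24. Survival is also part of the primary outcome. The set is therefore selected, after randomization, on a component of the endpoint that it is used to analyse, and the patients removed for dying are all failures.

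Two features of the trial make this more than a formality. The Background states that "graft loss in elderly patients is predominantly associated with patient’s death with a functioning graft", so death is a leading route to failure in this population. And because loss to follow-up is expected to be negligible and patients who stop their regimen stay in the study, death would be a main reason for not completing.

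At stake is the per-protocol result for the primary endpoint. It would overstate success in both arms and, if mortality differs between arms, would credit the arm with more deaths. The rationale for the trial includes the raised infection-related mortality and malignancy of elderly recipients under current immunosuppression, so a mortality difference in either direction is a possibility the analysis should handle.

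**Working it through.** **Inputs from the article (Sample size):** expected success 48% (TMP) and 62% (TEP); 187 patients per arm; one-sided test; power at least 0.86. Alpha is not stated; 0.05 is assumed.

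**The plan's own figure.** Two-proportion normal approximation with pooled variance under the null:
- null SE = √(2 × 0.55 × 0.45 / 187) = 0.0515
- alternative SE = √((0.48 × 0.52 + 0.62 × 0.38) / 187) = 0.0509
- power = Φ((0.14 − 1.645 × 0.0515) / 0.0509) = 0.861

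This reproduces the stated power. The sample size is not affected by the present point.

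**Assumption.** The documents give no death rate, so two-year death shares d of 5% to 20% are used. Other exclusions from the set are taken to be unrelated to outcome.

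**Formula.** Every death is a failure, so removing deaths leaves the number of successes unchanged and shrinks the denominator:

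per-protocol success = p / (1 − d)

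**One arm, p = 48%:** d = 5% gives 50.5%; d = 10% gives 53.3%; d = 15% gives 56.5%.

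**Two arms, true success 48% in both (true difference 0):**

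| Deaths, arm 1 | Deaths, arm 2 | Per-protocol, arm 1 | Per-protocol, arm 2 | Arm 2 − arm 1 |
|---|---|---|---|---|
| 5% | 5% | 50.5% | 50.5% | 0 |
| 5% | 10% | 50.5% | 53.3% | +2.8 points |
| 10% | 15% | 53.3% | 56.5% | +3.1 points |
| 8% | 14% | 52.2% | 55.8% | +3.6 points |
| 5% | 15% | 50.5% | 56.5% | +5.9 points |
| 10% | 20% | 53.3% | 60.0% | +6.7 points |

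Differences are taken before rounding. Swapping the arms reverses the sign. With deaths kept as failures, every difference is 0.

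**Chance of a false one-sided 5% result for the arm with more deaths.** Same test, with 187(1 − d) patients per arm. For 10% versus 15%: 168.3 and 158.95 patients, pooled rate 0.5486, null SE 0.0550, alternative SE 0.0550, so Φ((0.0314 − 1.645 × 0.0550) / 0.0550) = 0.14. For 5% versus 10%, 5% versus 15% and 10% versus 20% the values are 0.13, 0.29 and 0.33. These are approximations, because the plan uses a mixed model adjusted for stratum and centre.

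**The order can reverse.** True success 46% with 12% deaths against 48% with 5% deaths: 0.46/0.88 = 52.3% against 0.48/0.95 = 50.5%.

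**Under the planned 48% versus 62%:**
- 5% deaths in each arm: 50.5% versus 65.3%, a difference of 14.7 points
- 10% deaths in each arm: 53.3% versus 68.9%, 15.6 points
- 12% deaths in TMP and 5% in TEP: 0.48/0.88 = 54.5% versus 0.62/0.95 = 65.3%, 10.7 points

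The rule can therefore also understate a real benefit.

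**The case against.** Four objections deserve an answer.

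**The intention-to-treat result is sound.** It keeps every death as a failure. The trial asks whether the adapted regimen improves outcome, and nothing ties its conclusion or sample size to the per-protocol set. This stands and sets the weight of the point. A reader might infer that the trial's main result is compromised; the text does not support that.

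**Completion is undefined.** A patient followed until death could be counted as a completer, and the full protocol or analysis plan may say so. That reading is possible, but nothing in the article supports it, and the article states a rule rather than leaving one open. If that is the intention, the sentence needs to say so.

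**The size rests on assumed deaths.** This also stands. No passage gives a death rate or suggests an imbalance, and with equal deaths and no true difference the comparison is unbiased. Death, graft loss and low eGFR are also reported as individual endpoints at 12 and 24 months, so a marked mortality imbalance would be visible beside the per-protocol result, although that would not correct it.

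**Graft loss is a different case.** It is tempting to infer that patients who lose the graft are dropped as well. No passage says that they leave. Patients who stop the regimen remain in the study, and even after consent withdrawal the team will ask to obtain creatinine and dialysis data. The point is limited to deaths. Nor does the article say how much weight readers should give the per-protocol result, so none is claimed here.

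**Conclusion.** The point holds for deaths, on the ordinary reading of completion. The per-protocol set selects on a component of the primary endpoint: success is inflated from p to p/(1 − d), and unequal deaths shift the comparison towards the arm with more of them. In the central example (48% true success in both arms, deaths of 15% versus 10%) the spurious difference is 3.1 points, against a design difference of 14 points; over the death shares tried, it runs from 0 to 6.7 points. These sizes depend entirely on assumed mortality. The direction is not fixed in advance, since it depends on which arm has more deaths.

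This is a should-fix for a supporting analysis. The intention-to-treat analysis and the sample size are unaffected.

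**What to change.** Delete the completion requirement. Define the per-protocol set as patients who met the eligibility criteria and had no major protocol deviation up to month 24, death or graft loss, whichever comes first. State that patients who die or lose the graft without an earlier major deviation stay in the set as failures. Naming graft loss settles its handling as well.

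The cost is one sentence of analysis wording before database lock, with no new data and no additional patients. There is a small downside: the set still conditions on adherence after randomization, and patients with early events have less time in which to deviate. The per-protocol result should therefore be labelled as supportive of the intention-to-treat result.

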### Trial status

The trial started in July 2019. On 01-04-2021, all centers had started and a total of 116 patients were included: 64 in stratum A and 52 in stratum B. A total inclusion time of 4 years was foreseen, based on the number of transplantations in the years 2014–2016, and the consent rate of other trials. However, due to the COVID-19 pandemic study inclusion will be delayed, although the extent is unclear yet.

## Discussion

Here we describe the design of the OPTIMIZE study; a trial that compares two immunosuppressive regimens in 374 *de novo*, elderly KTR.

Elderly patients make up one third of the total population of KTR in The Netherlands and have different characteristics when compared to younger recipients. Elderly recipients experience less rejection related graft loss, but more immunosuppression-related graft loss. We felt that it was of utmost importance to conduct a randomized clinical trial that may lead to optimization of the immunosuppressive treatment – and thereby, better outcomes - for this large, and growing, distinct population.

Our study design resembles that of the TRANSFORM study. As described above, in this study no difference in kidney transplant function was observed at two years after transplantation. To enhance the chance of reaching a difference in the primary outcome between the two groups, we aim for lower tacrolimus trough concentrations in the TEP (= reduced CNI) group than was intended in the TRANSFORM study. We aim for levels of 5–7 ng/ml during months 0–3, 2–4 ng/ml (instead of 2–5) during months 3–6, and 1.5–4 ng/ml (instead of 2–4) thereafter. We will closely review the tacrolimus trough concentrations for all patients on a monthly basis to ensure that target levels are achieved in our study.

Our primary endpoint is ‘successful transplantation’. We did not include tBPAR in the primary endpoint. Several studies have already shown that the risk for acute rejection in the elderly is low, especially when the kidney is from a younger donor (< 65 years) or from an elderly (≥ 65 years) donation after brain death donor [1, 23]. Because we examine a low to medium risk population, we expect the acute rejection risk to be even lower in our elderly population. Additionally, the TRANSFORM study already showed that rates of tBPAR did not differ between the reduced- and standard CNI group. tBPAR was therefore included as a secondary endpoint only.

One of the ‘standard’ secondary endpoints is the evolution of renal function over time by slope analysis. We will use both eGFR and creatinine clearance, based on the 24-hour urinary excretion of creatinine. A recent study showed that, surprisingly enough, inhibition of mTORC1 in sarcopenic rats counteracted sarcopenia, as determined by observing an increase in muscle mass [24]. Although this has not been studies in humans, we hypothesize that everolimus may lead to an increase in muscle mass, which can be reflected by a rise in the serum creatinine and a drop in the eGFR. This and the frequently observed increase in muscle mass in transplant recipients is why we feel that using the eGFR alone for assessment of evolution of kidney function over time might not be sufficient.

In addition to some ‘standard’ secondary endpoints, we will pay special attention to frailty and health-related quality of life of the elderly KTR. This will increase our knowledge on the benefits and risks of transplantation in elderly patients and will better fit the outcomes of interest for older patients. We will use the trial data to assess the cost-effectiveness of the TEP-regimen, compared to the TMP-regimen.

This study will also provide information on the function of the aged immune system after kidney transplantation and the associated effect of the two different drug regimens. We aim to identify immunologic parameters that may serve as biomarkers of immunosenescence for future clinical application.

We want to mention a few limitations of our study. The first one is that the trial is not powered for differences of smaller than 14 % between the two groups for the primary endpoint ‘successful transplantation’. However, this was a deliberate choice; the study group decided that differences below 14 % would probably not be clinically relevant. The second one is that the study is not blinded. As we need to adjust the dose of the study medication according to the trough concentrations, unfortunately, blinding is nearly impossible. A third limitation is the fact that induction with T cell-depleting therapy is not allowed. This is because induction with T cell-depleting therapy is not part of standard practice in this vulnerable patient group in the Netherlands and Belgium.

## Conclusions

The OPTIMIZE study is a unique clinical trial; it is the first randomized clinical trial to extensively examine the effect of a low exposure tacrolimus regimen in combination with everolimus specifically in *de novo* elderly kidney transplant recipients. The study also pays attention to the quality of life, cognitive and physical functioning of the participants. The unique character of the study in combination with the data it will yield will position the OPTIMIZE study to have a profound impact on future kidney transplant practice in elderly recipients.

## Data Availability

The datasets used and/or analysed during the current study are available from the corresponding author on reasonable request.

## Abbreviations

KTR: Kidney transplant recipients
ESP: Eurotransplant Senior Program
CNIs: Calcineurin inhibitors
HIV: Human immunodeficiency virus
HBsAg: Hepatitis B surface antigen
HVC: Anti-hepatitis C virus (HCV)
TMP group: Tacrolimus, mycophenolate mofetil, prednisolone group
TEP-group: Tacrolimus, everolimus, prednisolone group
TAC: Tacrolimus
CsA: Cyclosporine A
BAX: Basiliximab
RND: Randomization
EVR: Everolimus
HBV: Hepatitis B
eGFR: Estimated GFR
tBPAR: Treated biopsy-proven rejection
PBMCs: Peripheral Blood Mononuclear Cells
DSA: Donor-specific anti-HLA antibodies
CFS: Clinical Frailty Scale
*SF-12*: Short Form − 12
EQ-5D: European Quality of life-5 Dimensions
B-IPQ: Brief Illness Perception Questionnaire
DSI: Dialysis Symptom Index
MTSOSD-59: Modified Transplant Symptom Occurrence and Symptom Distress Scale-59
FFI: Fried Frailty Index
MoCA: Montreal Cognitive Assessment
SPPB: Short physical performance battery
BAASIS: Basel Assessment of Adherence to Immunosuppressive Medication Scale
